### Implementation

The researcher generates an allocation sequence and assigns interventions according to the sequence concealed in sealed, sequentially numbered envelopes, which are opened only at the allocation time point. Participants are informed of group assignment on day 30 (intervention delivery) for the experimental group or at close-out for the control group.

### Seasonal Control

To account for seasonal or environmental factors over the 15-month recruitment window, device assignment ensures equal representation from both groups at each time point. An even number of participants receive devices simultaneously, preventing differential seasonal effects between groups.

### Blinding (Masking) Level

This is an open-label pilot trial with partial blinding where feasible. Participants become aware of group assignment at different time points (experimental group participants are informed on day 30 at intervention delivery; control group participants are informed on day 60 at close-out). Samsung Galaxy Watch 4 automatically records objective sleep data independent of participant or researcher knowledge, eliminating measurement bias for the primary outcome. The researcher analyzing primary outcome data (Samsung scores) remains blinded to group allocation, and unblinding occurs on day 30 to identify participants for analysis in the experimental group in order to provide personalized recommendations.

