#### Experimental Intervention: Personalized ML-Derived Recommendations

Experimental group participants receive personalized behavioral recommendations from a predefined library (Multimedia Appendix 1) on day 30 based on individual ML model analysis of their baseline sleep data (days 1‐30).

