### Model Architecture and Development

The 15 Samsung Galaxy Watch 4 explanatory variables and additional engineered features serve as the base dataset. The training-validation framework involves a temporal split using baseline period data (days 1‐30) with a 70/30 split for training/validation, cross-validation through 5-fold time-series cross-validation to prevent data leakage, and individual modeling for separate models trained for each participant. Models include random forest regression (primary model for interpretability), gradient boosting (extreme gradient boosting [XGBoost]) for comparison, and multiple linear regression as baseline, with selection based on cross-validation root mean square error and R². Feature importance and selection involve SHAP values for feature importance ranking, recursive feature elimination to identify the top 5 predictors per participant, and correlation analysis to avoid multicollinearity (threshold: *r*>0.8). Personalized recommendation generation is based on individual feature importance ranking, and participants receive targeted recommendations from a predefined library (Multimedia Appendix 1), with a focus on their top 2‐4 modifiable sleep parameters.

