### Personalized Sleep Intervention Framework

The intervention content is based on individual ML feature importance ranking, and participants receive nonpharmacological recommendations from a predefined library (Multimedia Appendix 1) targeting their top 2‐4 predictive sleep parameters [108-116]. Example recommendations for TST optimization (if sleep_duration is a key predictor) are as follows: ensure wake-up time commitment for too much sleep and bedtime commitment for too little sleep. Example recommendations for sleep efficiency enhancement (if movement_awakening is a predictor) are as follows: use white noise, ensure a quiet environment, and restrict caffeine intake (avoid intake ≤6 hours before bedtime). Example recommendations for sleep timing regulation (if sleep_cycle is a predictor) are as follows: ensure a consistent sleep-wake schedule and keep the bedroom cool (around 18 °C‐20 °C).

Experimental group participants receive personalized recommendations, and the top 2‐4 recommendations are explained by the researcher during the in-person meeting. Adherence tracking involves self-reported compliance assessed at study closure (0%‐100% scale). Control group participants receive generic sleep hygiene education without personalization by the researcher during the in-person meeting.

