### ML-Derived Heterogeneity by Design

Personalized interventions intentionally create between-participant variability within the experimental group, and this is the intervention’s defining feature, not a statistical flaw. Participant A might receive recommendations targeting REM sleep and sleep timing, while participant B might receive advice on deep sleep and wake episodes, based on individual ML model findings. This heterogeneity is the core innovation: targeting individual-specific parameters rather than universal protocols.

With regard to statistical implications, within-group variance in the experimental arm may exceed variance in the control arm. This reduces statistical power but reflects real-world personalization implementation. If personalization is effective, the increased precision of targeting individual needs should overcome variance increases. If personalization shows no benefit despite this heterogeneity, the approach is not superior to simpler generic advice. We do not attempt to statistically “control for” intervention heterogeneity, as it represents the intervention. Exploratory analyses will descriptively examine whether certain recommendation types (eg, duration-focused vs architecture-focused recommendations) show differential effectiveness, informing future research on personalization boundaries.

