#### Exploratory Analyses: Hypothesis Generation Only

The exploratory analyses involve the following three aspects:

Individual parameter changes: Compare the change in specific sleep variables (duration, deep sleep percentage, and REM percentage) between groups using *t* tests (unadjusted for multiple comparisons, given the exploratory nature).Adherence subgroups: In the experimental group, compare outcomes between high (≥80%) and low (<80%) self-reported adherence using the Mann-Whitney *U* test.Predictive feature patterns: Perform a descriptive analysis of which sleep parameters are most frequently identified as the top predictors across participants.

All exploratory analyses are labeled hypothesis-generating, not confirmatory. No adjustments are made for multiple comparisons, given the pilot scope of the study. Regarding the handling of missing data for the primary outcome (sleep score), participants are excluded if sufficient night data are not available in the baseline and postintervention periods, and action on the secondary outcome (PSQI) is derived from the handling of the primary outcome. This protocol contains the complete statistical analysis plan, and no separate statistical analysis plan exists.

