### Conclusions

This pilot study establishes the feasibility and preliminary evidence base necessary for future definitive trials testing whether ML personalization involving consumer wearable data can improve sleep outcomes. The manufacturer-independent framework, dual validation approach (objective device metrics plus subjective PSQI), and explicit pilot design appropriately position this study as hypothesis-generating research that could inform the next generation of personalized digital health interventions for sleep quality optimization in healthy populations.

The proposed approach tests a specific mechanistic hypothesis: precision targeting of high-impact parameters identified through individual ML models may enhance motivation through personalized predictions while reducing cognitive burden compared with generic recommendation lists. Rather than providing universal sleep hygiene advice, this methodology will generate interventions tailored to each participant’s unique sleep architecture patterns and predictive factors.

Building upon foundational work establishing wearable feasibility for sleep monitoring [36,71,105-107], this study’s planned contribution to the field involves testing whether ML-derived personalization improves outcomes compared with generic sleep hygiene. If the methodology proves feasible and preliminary effect sizes suggest a benefit, the resulting dataset of 1920 nights will enable iterative model refinement and provide evidence for scaling personalized sleep interventions to larger populations.

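### Targets and recommendation types appear to be set only in the experimental arm, so the look at which type works has no control counterpart and no planned analysis tests targeting itself

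*Protocol article*

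**What the plan says.** **Who gets advice and who is modelled.** Under Experimental Intervention, "Experimental group participants receive personalized behavioral recommendations from a predefined library" on day 30, based on a model of their own baseline nights. Blinding (Masking) Level says that "unblinding occurs on day 30 to identify participants for analysis in the experimental group in order to provide personalized recommendations". Model Architecture and Development describes "individual modeling for separate models trained for each participant" without naming an arm. Measurement Time Points has both arms supplying the same 30 baseline nights.

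**How targets are chosen.** Model Architecture and Development uses "SHAP values for feature importance ranking" together with recursive feature elimination, and narrows the result to two to four modifiable parameters. Personalized Sleep Intervention Framework gives an example in which the direction of the advice depends on the person's own level: "ensure wake-up time commitment for too much sleep and bedtime commitment for too little sleep".

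**What is analysed.** ML-Derived Heterogeneity by Design states: "Exploratory analyses will descriptively examine whether certain recommendation types (eg, duration-focused vs architecture-focused recommendations) show differential effectiveness". Exploratory Analyses lists a plan to "Compare the change in specific sleep variables (duration, deep sleep percentage, and REM percentage) between groups" by t test. That section also says that the article holds the whole statistical analysis plan and that no separate one exists. The primary analysis is a randomized ANCOVA of mean sleep score with the baseline score as covariate.

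**What is claimed.** The Conclusions put forward as the hypothesis under test that "precision targeting of high-impact parameters identified through individual ML models may enhance motivation through personalized predictions".

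**The concern.** The distinctive claim is that aiming advice at each person's own influential parameters helps. The direct check is whether the targeted parameters move more in people who were told about them than in comparable people who were not. That needs control participants whose targets are known but undisclosed, and the plan defines no such targets.

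The look by recommendation type then compares subgroups inside one arm. Type is not randomized; it comes out of each participant's baseline data. People given duration advice differ beforehand from people given architecture advice, and those flagged for an unusually low value may drift back without any advice. The protocol wants this look to inform where personalization works and where it does not, and it expects the dataset to show which parameters respond most reliably. An uncontrolled contrast could point the proposed 350-participant trial at the wrong parameters.

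**Working it through.** The plan states no figure for this point, so there is none to reproduce.

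**1. Scope of modelling.** The advice goes to the experimental arm only, and the day 30 unblinding is described as picking out experimental participants for analysis. Read together, these mean that controls are not modelled. Against that, the model-building section says each participant, and the planned tally of top predictors names no arm. Experimental-only modelling is therefore an inference. On either reading, however, no section gives controls a target set or a recommendation type, or uses one in a comparison.

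**2. The look by type.** With types present in one arm only, the observed change after type k = effect of the advice + untreated change in the people assigned type k. Nothing in the plan estimates the second term.

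**3. How large the second term could be.** For a standardized parameter, expected untreated change = (1 - r) x (distance of the selected people's baseline below the mean). Here r is the correlation between the two 30-night means. The documents do not give r; Pilot Objectives lists it as something to be learned. A null simulation (no intervention effect, 16 per arm, 6 independent parameters, 3 targets each, 3000 replicates) gave these results for apparent improvement in targeted parameters in the experimental arm alone:

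| How targets are chosen (assumed) | r = 0.6 | r = 0.8 | r = 0.9 |
|---|---|---|---|
| Independent of baseline level | 0.00 SD | 0.00 SD | 0.00 SD |
| Partly by low baseline | 0.16 SD | 0.08 SD | 0.04 SD |
| Wholly by low baseline | 0.28 SD | 0.14 SD | 0.07 SD |

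The last row agrees with the formula: 0.281/0.4 = 0.70, 0.140/0.2 = 0.70 and 0.071/0.1 = 0.71, so the chosen parameters sat about 0.7 SD below the mean.

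When controls were given targets by the same rule, the experimental-minus-control difference lay between -0.002 and 0.008 SD in every setting. The spurious component cancels.

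**4. The whole-arm parameter comparisons.** In the same simulation the between-arm t test on a fixed parameter rejected in 4.4% to 5.4% of null trials, against a nominal 5%. Regression to the mean is equal in expectation in both arms, so these tests are sound.

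What they estimate is an average: observed difference = p x (effect in those targeted), taking no effect in the others, where p is the share of the arm targeted on that parameter. As an illustration, take 3 targets spread evenly over 6 to 15 candidates (15 is the number of model inputs). Then p = 3/6 = 50% down to 3/15 = 20%, and a targeted effect of 0.8 SD would show as 0.8 x 0.50 = 0.40 SD down to 0.8 x 0.20 = 0.16 SD. The even spread and the 0.8 SD are assumptions.

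**5. Precision of a controlled look by type.** With about 5 people per arm in a type (assumed), SE of the difference in change = sqrt(2(1 - r)) x sqrt(2/5). This gives 0.28, 0.40 and 0.57 SD for r = 0.9, 0.8 and 0.6.

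**The case against.** The strongest reply has four parts.

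- **Target choice is not selection on low values.** Parameters are ranked by feature importance. The duration example runs in both directions, and the types are grouped by focus rather than direction, so regression upward and downward would partly cancel. This stands. A reader might take the lowest third on a parameter as the selected group, which gives (1 - r) x 1.09 = 0.11 to 0.44 SD for r from 0.9 to 0.6. No selection rule of that kind is documented, so those figures should not be used. What remains without any regression to the mean is that people given different types are different people.
- **The parameter t tests do their stated job.** The exploratory outcome is which variables improve, and a randomized whole-arm comparison answers that. A reader might infer that regression to the mean spoils these tests too. It does not, and they should stay.
- **Everything here is labelled descriptive or hypothesis-generating, and the limitations section says that the sample restricts subgroup analyses.** True, and it lowers the weight of the point. But the label does not supply the missing comparison group, and these looks are meant to guide later research.
- **The remedy is imprecise.** Each standard error in step 5 exceeds the largest simulated spurious change at the same r (0.07, 0.14 and 0.28 SD). Human review and participant feedback may also alter the advice delivered, so pipeline targets will not match it exactly. Both points stand. They limit what the added analysis can show, but do not favour having no control.

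**Conclusion.** The point holds in a limited form. As planned, the look by recommendation type lacks a concurrent control and cannot tell the effect of the advice from the make-up of the groups. No planned analysis compares change in a person's own targeted parameters between arms, although targeting is the stated hypothesis. The contribution of regression to the mean is unknown. It is zero if targets and advice direction are independent of baseline level, and it reached 0.28 SD only under the extreme assumed setting of selection wholly by low baseline with r = 0.6.

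Two stronger conclusions are not supported. The documents do not say outright that control models are never fitted. Nor is the main question compromised: the baseline-adjusted, randomized comparison of personalized with generic advice is untouched. Nothing is lost for good either, because control baseline nights are collected and kept. This is a low-to-moderate weakness in the exploratory part of the plan, worth correcting because correction is cheap.

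**What to change.** 1. In Model Architecture and Development and in Blinding (Masking) Level, state that one frozen pipeline (code, seeds, and the rules that turn rankings into targets, direction and type) is run on the days 1-30 data of all 32 participants. For controls this can be done retrospectively, and the output is not delivered. Store each person's pipeline targets and type.
2. In Exploratory Analyses, keep the existing t tests. Add an experimental-versus-control comparison of change in each participant's own pipeline-assigned targets, in SD units of the parameter, signed in the recommended direction and adjusted for baseline.
3. Report the look by type in ML-Derived Heterogeneity by Design as experimental versus control within the same pipeline-assigned type, with intervals.
4. Use pipeline output, not delivered advice, to define targets in both arms, because the advice may be changed by the researcher's review or at the participant's request.

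Cost: computing for 16 more sets of models on data already held, and some rewording. No visits, participants or new data are needed. Intervals within types will be wide, the match between pipeline targets and delivered advice will be imperfect, and the results remain hypothesis-generating.

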### Justification for Partial Blinding

Complete participant blinding is impossible for providing personalized and generic advice. The primary outcome (device-recorded sleep score) has objective measurement protection. For the secondary outcome (PSQI), assessor blinding is attempted where feasible. This pragmatic approach balances methodological rigor with pilot study feasibility.

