### Outcomes

#### Primary Outcome: Mean Samsung Galaxy Watch 4 Sleep Score During the Postintervention Period

We are working within proprietary constraints. We use the Samsung sleep score (1-100 scale) as the primary outcome for the following reasons: (1) real-world relevance: the score is the metric users see and seek to optimize in consumer wearable ecosystems; (2) continuous sensitivity: the scoring scale (1‐100) detects individual-level changes with precision, which categorical systems cannot achieve; (3) composite integration: the score algorithmically combines multiple sleep dimensions (duration, architecture, efficiency, and fragmentation), providing a holistic optimization target; (4) feasibility for personalization: continuous data for 60 nights enable individual ML models to identify predictive patterns; and (5) validation through correlation: secondary PSQI outcomes confirm that objective score improvements correspond to subjective sleep quality perception.

There are some limitations. The use of a proprietary algorithm limits the reproducibility of exact score computation. Moreover, there is no PSG validation of the composite score specifically (though component parameters are validated [36-43]). Furthermore, the manufacturer-specific metric precludes direct cross-device comparisons. These limitations are inherent to consumer wearable research and do not invalidate the personalization methodology (they contextualize the interpretation). Our framework is designed to work *within* these pragmatic constraints while remaining transferable to other manufacturers’ proprietary systems.

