#### Secondary Outcome: PSQI Global Score Measured at Three Time Points

The PSQI (0-21 scale) validates that objective sleep score improvements correspond to the subjective perception of sleep quality and functional impact, ensuring clinical relevance from the patient perspective. The PSQI is not used as a competing primary measure but rather as a tool to provide complementary validation that device-measured changes reflect meaningful improvements in lived experience.

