### Data Collection Quality Control

The following measures are implemented for user-related issues: (1) noncompliance: participants with missing data for >20% of nights are excluded and replaced; (2) charging issues: backup chargers are provided, and daily battery monitoring is required; (3) unauthorized modifications: settings are locked, and violations lead to replacement; and (4) sync delays: daily commitment for cloud backup within 24 hours. The following measures are implemented for device-related issues: (1) fragmented recording: nights without combined scores are excluded; (2) data mismatch: nights with artifact conflicts are excluded; and (3) sync errors: multiple attempts are made with escalating intervals. For sensor inaccuracies, quality control is performed through sleep diaries, and outliers trigger replacement. Excluded participants are replaced from the recruitment pool to maintain the sample size. The expected night exclusion impact is around 18%, with anticipated replacement ensuring the target sample.

Subjective data collection is performed through PSQI forms completed on paper. Information is manually entered by the researcher into a password-protected spreadsheet with self-verification (data are entered twice by the researcher to ensure accuracy). Data are processed through the manufacturer’s algorithms to interpret the findings of the 10 explanatory variables and the target variable (Table 1).

**Table 1. T1:** Target and explanatory variables collected by the wearable (indispensable for this study).

Variable		Description	Unit	Data type
Explanatory variable				
sleep_duration		Sum of N1, N2, N3, and REM^a^	Minutes	Integer
movement_awakening		Count of movement during sleep	Number	Integer
sleep_cycle		Count of sleep cycles	Number	Integer
mental_recovery		Score assigned according to the REM phase	Score (0‐100 scale)	Integer
physical_recovery		Score assigned according to the N3 phase	Score (0‐100 scale)	Integer
efficiency		real_total_sleep by sleep_duration	Percentage	Integer
Transition_N1		Sum of minutes of sleep in the N1 phase	Minutes	Integer
Light_N2		Sum of minutes of sleep in the N2 phase	Minutes	Integer
Deep_N3		Sum of minutes of sleep in the N3 phase	Minutes	Integer
REM		Sum of minutes of sleep in the REM phase	Minutes	Integer
Target variable				
sleep_score		Score assigned for the night	Score (1‐100 scale)	Integer

a REM: rapid eye movement.

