#### Compensation for Research-Related Injury

In the unlikely event of research-related injury, immediate medical care coordination will be provided by the researcher, participants can use existing health insurance for treatment, no additional compensation will be provided, and the incident will be documented and reported to the ethics committee. The anticipated risk is minimal (behavioral intervention, noninvasive device use, skin irritation from the device, sleep tracking anxiety, and time commitment).

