### Study Strengths

Despite these limitations, this pilot study has several strengths. The manufacturer-independent framework provides a transferable methodology applicable across platforms, potentially driving the field toward less proprietary and more user-centered approaches. The dual validation combining objective and subjective measures addresses both physiological and patient-reported domains. The explicit pilot design appropriately positions findings as preliminary and hypothesis-generating rather than making premature efficacy claims. The comprehensive data governance framework (local-only storage, multilayer anonymization, and explicit AI accountability measures) provides a model for ethical wearable research. The transparent reporting approach with public data sharing enables replication and meta-analytic integration regardless of the findings.

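### Assessor blinding cannot protect a self-reported PSQI in this open-label, single-researcher trial, so the PSQI can support but not confirm the score change

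*Protocol article*

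**What the plan says.** Under Justification for Partial Blinding, the protocol article concedes that participants cannot be fully blinded and credits the device score with objective protection. For the PSQI it says: "For the secondary outcome (PSQI), assessor blinding is attempted where feasible".

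Data Collection Quality Control describes how the PSQI is gathered: "Subjective data collection is performed through PSQI forms completed on paper". The researcher then enters the answers twice. Study Setting places PSQI administration in face-to-face meetings with a researcher.

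On knowledge of allocation, Blinding (Masking) Level says: "experimental group participants are informed on day 30 at intervention delivery; control group participants are informed on day 60 at close-out".

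The article gives the PSQI a validating role in three places:
- Primary Outcome: "secondary PSQI outcomes confirm that objective score improvements correspond to subjective sleep quality perception".
- Secondary Outcome, where it serves "as a tool to provide complementary validation that device-measured changes reflect meaningful improvements in lived experience" and is also said to ensure clinical relevance.
- Study Strengths: "The dual validation combining objective and subjective measures addresses both physiological and patient-reported domains".

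Secondary Analysis: PSQI Changes specifies an independent-samples t test on the day 0 to day 60 change and a Pearson correlation between score change and PSQI change. It does not say whether the correlation takes account of arm. The article states that it holds the complete analysis plan and that no separate one exists.

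**The concern.** Blinding an assessor protects an outcome that the assessor rates. Here the participant supplies the rating, and someone who knows that they hold personalized, algorithm-derived advice may report better sleep for that reason alone. Blinding whoever hands out or enters the form cannot remove that.

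This matters because the article leans on the PSQI. It concedes that the proprietary composite score has no polysomnographic validation of its own, and it turns to the PSQI to show that a score change means something to the sleeper. If the PSQI can move through expectation in one arm only, a between-arm PSQI difference does not independently corroborate the score. Neither Study Limitations nor the Conclusions mention reporting bias in the PSQI.

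**Working it through.** **1. Is there a blinded assessor?** The relevant sections, side by side:
- Implementation: the researcher generates the sequence and assigns the interventions.
- Intervention Delivery and Verification, and Personalized Sleep Intervention Framework: the researcher explains the advice in person.
- Blinding (Masking) Level: unblinding occurs on day 30 so that the experimental recommendations can be produced.
- Data Collection Quality Control: the researcher enters the PSQI data.
- Data Management: nobody else has access to the data.

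No second person is described who could administer, score or enter the day-60 PSQI without knowing allocation.

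**2. Which PSQI is affected?** The day-0 form precedes device use. Measurement Time Points lists the day-30 form ahead of intervention delivery, where the experimental arm is told its group. The exposed measurement is therefore day 60, which enters the change score in the t test. Measurement Time Points lists the PSQI and then the closure interview for that day, but sets no rule that the PSQI comes before disclosure to controls.

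**3. Calibration on the plan's own figure.** The plan states power above 80% for d of 1.0 or more with 16 per arm. For a t test with df = 2×16 − 2 = 30 and noncentrality d × √(16/2), power at d = 1.0 is 86.8% one-sided and 78.1% two-sided (normal approximation: 88.2% and 80.7%). The figure reproduces under the one-tailed test stated for the primary analysis. The present point does not depend on it.

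**4. Exposure of the PSQI t test.** Let b be the net reporting bias between arms, in SDs of PSQI change, with no true effect. The documents give no value for b, so a range is shown. Noncentrality = b × √8 = 2.828b, and the two-sided critical t on 30 df is 2.042. For b = 0.5, noncentrality is 1.414. The protocol does not state the sidedness of this test, so both are given; one-sided means in the direction of the bias.

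| Assumed b (SD) | Significant, two-sided .05 | Significant, one-sided .05 |
|---|---|---|
| 0 | 5% | 5% |
| 0.2 | 8.5% | 14% |
| 0.3 | 13% | 21% |
| 0.5 | 28% | 40% |
| 0.8 | 59% | 71% |

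**5. Exposure of the correlation, if pooled.** Suppose there is no association within arms, allocation is 1:1, and the arms differ by d1 SD on score change and d2 SD on PSQI change. Then

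|r| = 0.25·d1·d2 / √[(1 + 0.25·d1²)(1 + 0.25·d2²)].

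- d1 = d2 = 0.3: 0.0225 / 1.0225 = 0.02.
- d1 = d2 = 0.7: 0.1225 / 1.1225 = 0.11.

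The range 0.3 to 0.7 is what the protocol calls typical in sleep research. Because a higher PSQI is worse, a favourable shift on both measures gives a negative r. For comparison, the 95% interval around r = 0 with n = 32 is tanh(±1.96/√29) = ±0.35. The artefact in the correlation is small beside sampling error, so the t test is the greater worry.

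**The case against.** Much is already disclosed. The trial is labelled open-label, participant blinding is conceded to be impossible, only the primary outcome is credited with objective protection, the PSQI is called complementary, and all findings are labelled preliminary. The blinding sentence is hedged. Blinding whoever administers or enters a self-report form would also be of some use. That stands as far as it goes: nothing is concealed, and the outcome is a supporting one in a pilot. It does not supply a blinded assessor where one person holds every role, and it does not license the word *confirm*.

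Three stronger readings are tempting, but the documents do not support them.

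- **Both arms know their group during follow-up.** Controls know what advice they received, but they are formally told their group only at close-out. Knowledge during follow-up is documented for the experimental arm alone. Controls might guess, since consent describes the use of machine learning, but that is conjecture.
- **Participants rate the PSQI after seeing their nightly scores.** The article says "the score is the metric users see and seek to optimize in consumer wearable ecosystems", which describes consumer products in general. The listed risks, "skin irritation from the device, sleep tracking anxiety, and time commitment", do not show that scores were displayed either. Settings are said to be locked, and display to trial participants is not described. Any visibility could also apply to both arms.
- **Expectation alone could produce a significant pooled correlation.** With equal shifts, reaching 0.349 needs 0.25d² / (1 + 0.25d²) = 0.349, so d is about 1.46 in both measures. That is well above the 0.3 to 0.7 range, and the plan states no significance test for r.

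Experimental participants are shown plots of what drives their own score, but they are also told that these findings are correlational, so the plots should not be read as a promise of benefit.

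**Conclusion.** The concern holds in a limited form. The assessor-blinding statement describes a safeguard that the design does not have, and the validation wording claims more than an unblinded self-report can deliver. Timing of disclosure differs by arm, so differential expectation at the day-60 PSQI is possible. Its size is unknown. Assumed net biases of 0.2 to 0.8 SD would raise the two-sided false-positive rate of the PSQI t test from 5% to between 8.5% and 59%, with 28% at 0.5 SD. The effect on a pooled correlation is minor, about 0.02 to 0.11, and that assumes the correlation is pooled, which the text implies but does not state. The primary analysis, sample size and alpha are not affected.

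**What to change.** 1. In Justification for Partial Blinding, delete the assessor-blinding claim and describe the PSQI as an unblinded patient-reported outcome. Add differential reporting bias to Study Limitations.
2. In Secondary Analysis: PSQI Changes, compute the correlation between score change and PSQI change adjusted for arm (partial r). State in advance that the expected sign is negative. Show within-arm values descriptively.
3. Require the day-60 PSQI to be completed before group disclosure and before the closure interview. For visits already held, report the order used.
4. In the two outcome sections, replace *confirm* and *ensuring* with wording such as supportive and unblinded, and temper the dual-validation claim under Study Strengths and Conclusions to match.

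The cost is wording, one line of analysis and a rule on visit order. The partial r gives up one degree of freedom: its 95% interval around zero is tanh(±1.96/√28) = ±0.354, against ±0.349 unadjusted. Within-arm values with n = 16 are imprecise, at tanh(±1.96/√13) = about ±0.50, which is why they should stay descriptive.
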